#### Recruitment

Online advertisement of the pilot trial will be delivered through WeChat to different WeChat users. Potential participants who read the trial advertisement and were interested in participating could subscribe to the SCAMPI WeChat official account (OA). Once they subscribe to the account, they will receive an auto-replied trial instruction. People can tap the registration link on the instruction to register as a participant of the study.

In the registration system, potential participants will be screened to ascertain their eligibility for the study. Eligible participants will be provided with the participant information sheet and consent form for them to read. After they complete reading the documents, they will be asked to provide electronic consent (e-consent) by tapping the *agree* button.

Within the e-consent, participants will then be directed to complete the baseline assessment. A participant will receive his first study compensation once he completes the registration to strengthen his relationship with the study.

### Intervention

The SCAMPI program was designed using the behavior change wheel (BCW) framework, a theory- and evidence-based tool for designing interventions based on an analysis of the nature of the behavior, the mechanisms that need to be changed to bring about behavior change, and the interventions and policies required to change those mechanisms [20]. It is considered as one of the most inclusive behavior change framework that was developed from 19 frameworks of behavior change identified in a systematic literature review [20].

The BCW framework starts with a theoretical understanding of behavior by the *capability, opportunity, and motivation to behavior model* (COM-B model) to determine what needs to change for the behavioral target to be achieved and what intervention functions are likely to be effective to bring about that change [20]. After selecting the intervention functions most likely to be effective in changing the smoking behavior of the target population, these will then be linked to specific behavior change techniques (BCTs), which will be codable to a mobile social network–based smoking cessation program [21,22]. The content, user interface (UI), and user experience (UX) design of the SCAMPI program were developed based on the China Clinical Smoking Cessation Guideline (CCSCG) [23] and WeChat mini-program design guidelines [24].

The application of the BCW framework for developing the SCAMPI program was under a process called collaborative product development (CPD), which is based on the principles of user-centered design (UCD) developed by Preece et al in 2004 [25]. In this study, UCD occurred in 2 forms: (1) consulting users about their needs of the proposed mobile health app–based smoking cessation intervention and (2) involving users as partners with researchers throughout the design and development process [25].

In the CPD stage, 20 potential end users (Chinese male smokers aged 25 to 44 years) were recruited through WeChat. These 20 participants provided their ideas about the desired components of a smoking cessation program through completing a development questionnaire (Multimedia Appendix 1). In the 1-month period, app development progressed and relevant questions were posted on SCAMPI OA to identify participants’ preferences for the program’s UX and UI design. At the end of the CPD period, participants’ acceptability and satisfaction level toward the app were identified by completing an online questionnaire based on standard questions from the Mobile App Rating Scale (MARS) questionnaire (Multimedia Appendix 2) [26]. A total of 16 out of 20 participants completed the questionnaire, and the average rating of the SCAMPI program was 4.4 out of 5.0.

On the basis of the findings from participants’ responses to the development questionnaire and the behavior analysis of the target population’s smoking behavior [5,27], 11 key behavioral factors of the target population’s smoking behavior were summarized. These 11 factors reflect the 5 main components of the COM-B model. By applying the BCW to navigate the BCTs, 48 BCTs are relevant to these 5 reflected components of the COM-B model. Screening by the WeChat mini-program design guideline and the relevant context (eg, the program will be used by Chinese male smokers in China), 43 BCTs were considered as deliverable through the WeChat platform (Multimedia Appendix 3). Identified BCTs were integrated and coded as functions of the program. Table 1 shows the functions of the SCAMPI program and the corresponding BCTs that are aimed to be achieved by each function.

**Table 1 table1:** Functions of the program and corresponding behavior change techniques codes.

Functions	Corresponding behavior change techniques
Design of the program	RD^a^1
Calculator, data capturing, and recoding	BS^b^6, BM^c^9, RC^d^8, RI^e^1, RI2, RI3, and RI4
Calendar	BM3
Content of the program	RC1, RC4, and RC7
Game	BM5, BS4, BS5, and BS6
Informational and practical tool	BM1, BM10, BS1, BS2, BS10, A^f^5, RC5, RC6, RC10, BM8, BS10, BS7, BS8, BS11, and RD2
Motivation	BM2
Other	Health testers, red packet (compensation)
Planning	BS3
Social support	A2

^a^RD: general aspects of the interaction (R) focusing on the delivery of the intervention (D).

^b^BS: specific focus on behavior (B) and maximizing self-regulatory capacity or skills (S).

^c^BM: specific focus on behavior (B) and addressing motivation (M).

^d^RC: general aspects of the interaction (R) focusing on general communication (C).

^e^RI: general aspects of the interaction (R) focusing on information gathering (I).

^f^A: promote adjuvant activities (A).

In summary, besides the design and content, the SCAMPI program has the following functions: (1) calculator to record quitting benefits (eg, money saved by not smoking), (2) calendar to record the progress of smoking cessation (eg, which date the users did not smoke), (3) gamification to facilitate quitting (eg, ranking board for showing users who make the longest continuous smoking abstinence), (4) providing information about smoking harms and health benefits from smoking cessation, (5) sending motivational messages (based on requests from users) to help users overcome urges, (6) providing standardized tests to users for assessing their levels of nicotine dependence and lung health, (7) helping users to make smoking cessation plans, and (8) providing a social support platform to users for delivering peer support between users. Screenshots and Quick Response (QR) codes of the SCAMPI program are provided in Multimedia Appendix 4.

As the target users of the program will be Chinese male smokers, all contents of the program were designed to be in Chinese. Table 2 presents examples of database content by themes (eg, smoking harms and quitting tips). The database content is based on the taxonomy of BCTs for smoking cessation via a text messaging intervention [22]. The program database includes a pool of 40 articles about smoking harms, all of which are coded to be sent to users on a daily basis through the SCAMPI OA. Each of these articles may take less than 3 min for participants to read. Articles are presented in the form of text and images. Participants will be prompted to read the articles, and they can decide when to read the articles and if they want to re-read the articles. All articles will be stored in SCAMPI OA throughout the trial and after the trial is completed. Participants in both groups and other subscribers to the SCAMPI OA will be able to have access to these articles freely after the completion of the trial. Information on the articles was referred to the CCSCG [23]. In addition, the program was designed according to the WeChat mini-program design guidelines [24]. The principles of friendliness and courtesy, clarity, convenience and elegance, and consistency have been used in the UX and UI design of the program.

**Table 2 table2:** Examples of the program database content.

Themes	Examples of titles	Behavior change techniques
Smoking harms	“There are about 7,000 chemical components in tobacco, 69 of them are carcinogenic?!”	Provide information on consequences of behavior in general
Quitting tips	“When you feel urge to smoking, try deep breath and some physical exercise to distract your urge.”	Provide information on supporting behavior
Motivational messages	“Keep it up! You are XX days without smoking.”	Facilitate relapse prevention

Participants in the intervention group will have access to the full version of the SCAMPI program, and participants in the control group will have access to the restricted version of the SCAMPI program. Participants of the trial had free access to the SCAMPI program, both the full and the restricted versions. By the end of the trial, all WeChat users will have free access to the SCAMPI program. People can have access to the SCAMPI program by either search keywords “smoking or smoking cessation or SCAMPI” on the WeChat platform or scan the SCAMPI program QR codes.

### Compensation

Participants in both groups will receive weekly WeChat messages to remind them to enter their daily cigarette consumption. The compensation for participation was delivered in a form called WeChat red packet (*Hongbao*). In Chinese culture, red packet is a monetary gift that is given during holidays or special occasions such as weddings, graduation, or the birth of a baby [28]. The red color of the envelope symbolizes good luck and is a symbol to ward off evil spirits [28]. The WeChat red packet is a widely used online currency in China and is transferrable through the WeChat platform [28]. Recipients of the WeChat red packet can use the value of the red packet to purchase goods or use services in China [29]. The WeChat red packet will be provided to participants as compensation to enter the data as requested. Participants from both intervention and control groups will receive the same reminding message and the same WeChat red packet. There is no specific incentive for a particular group to provide their smoking status.

The compensation in this study will be given through 7 sessions (registration and 6 weekly data collection of cigarette consumption in the past week). Once participants complete each data entry session, the WeChat red packet pops out as compensation (participants in both groups receive the same WeChat red packet). The answers to the questionnaires had no impact on the value or form of the WeChat red packet participants (in both groups) received.

It has been proven that incentives may be able to give a useful improvement in reducing the quantity of missing data in trials [30-33]. A small financial incentive has minimal impact on the trial’s results [34]. In this trial, the financial value of the WeChat red packet provided to each participant (both groups) was ¥35 RMB (approximately US $4.93), which is considered as a small financial incentive [34]. Meanwhile, compared with traditional methods of incentive delivery (eg, courier post and cash), the WeChat red packet is more secure and convenient. The WeChat red packet was only used as a method to maintain the completion of questionnaires and retention of the trial. Upon completion of the 6-week follow-up, the full version of the SCAMPI program will be offered to participants in the control group.

### Procedures

The flow of participants’ experience in the trial is presented in Figure 1. After providing informed consent, participants will be randomly allocated to different groups (intervention and control group, n=40 in each group). Participants randomized to the intervention group will have access for 6 weeks to the full version of the SCAMPI program, and participants randomized to the control group will have access for 6 weeks to the restricted version of the SCAMPI program. On completion of the 6-week follow-up assessment, participants in the control group will be offered free full access to the SCAMPI program. All data on program use were recorded until the end of the trial.

**Figure 1 figure1:**
[figure not shown]
User experience in the trial.

All participation and procedures of the trial will be completed online through the WeChat platform. Participants who report themselves has 30-day continuous smoking abstinence at 6-week follow-up will receive a pack of cotinine test kit to test the nicotine levels of their saliva to biochemically verify their self-reported smoking abstinence.

Data of the trial will be collected online via the WeChat platform. Participants in both groups recorded their daily cigarette consumption for the week throughout the trial period. Usage data to the corresponding versions of the SCAMPI program were recorded by the server of the program. Participants’ baseline data and satisfaction with the program (for participants in the intervention group only) were collected through electronic questionnaires (registration questionnaire and end-of-trial questionnaire).

The registration questionnaire asked participants about their demographics, smoking status, willingness to quit smoking, and so on (Multimedia Appendix 4). The registration questionnaire was developed based on a national online survey about smoking behaviors of Chinese smokers [5,27]. The end-of-trial questionnaire (Multimedia Appendix 5) was developed and shaped based on a standard questionnaire, the MARS questionnaire [26]. It focuses on assessing users’ perception and satisfaction with the app or software or mobile program they used. Both questionnaires were overviewed and commended by experts from WeChat to ensure that their user experience met the Chinese users’ preferences.

### Retention

To prevent missing data, an effort will be made to retain the participants in the trial for the follow-up data collection. However, participants who withdraw their consent will discontinue their participation in the study. Participants who continue not entering their smoking status for 2 weeks will be considered as lost to follow-up. Participants who dropped out of the trial or who were lost to follow-up were considered to be smoking.

The strategies for improving the adherence to the study include the following: (1) gentle WeChat messages reminder—a weekly message will be sent to participants in both groups to remind them to enter the data about their daily cigarette consumption of the week, (2) participants in both groups will receive a WeChat red packet after they enter the data as requested, and (3) a button for *feedback* is available to participants in both groups on the main page of the SCAMPI OA. Participants were prompted to use text or voice messages to make their feedback or report their usage difficulties. Instant guidance to support participants to use the program will be provided by the program.

## Results

### Baseline Assessment

At the baseline assessment, the following data will be collected: age, marital status, employment status, family structure, age at smoking initiation, smoking cessation history, smoking status (consumption and frequency), and smoking cessation services usage history. These data will be collected at the beginning of the trial using an electronic questionnaire called the registration questionnaire (Multimedia Appendix 5).

### Primary Outcome Measure

The primary outcome of this pilot trial will be the participants’ biochemical verified 30-day smoking abstinence at 6-week follow-up. At the 6-week time point, researchers will review participants’ (in both groups) self-reported smoking status in the past 30 days to identify their self-reported 30-day smoking abstinence. The 30-day smoking abstinence is usually used as the primary outcome measure for smoking cessation intervention trials recommended by the Society for Research on Nicotine and Tobacco [35]. Quit failure was defined as any cigarettes smoked in the past 30 consecutive days. This measurement is also known as the 10th level of smoking abstinence in the Chinese standard for smoking cessation [23].

At the 6-week time point, a nicotine cotinine saliva test kit will be sent to participants (in both groups) who report themselves with 30-day smoking abstinence to verify their smoking abstinence status. These participants will be requested to complete the test at home (clear instruction provided) and upload a photo or a short video of the strip test results to the SCAMPI OA. The cotinine test has proven to be a valid and reliable method to test saliva samples for verification of smoking status [36,37].

### Secondary Outcome Measures

The secondary outcomes of the study included participants’ tobacco consumption changes through the trial period, retention of the trial, program (both versions) usage, and users’ satisfaction with the program (only for intervention group participants).

Tobacco consumption changes include measures of the following:

Participants’ cigarette consumption reduction: Participants will be required to provide their daily cigarette consumption (as a categorial range such as “1 to 5 sticks cigarettes per day”) at the baseline assessment. By using these data to compare with their daily smoking status through the pilot trial, researchers will be able to identify the reduction in cigarette consumption of participants (in both groups). Participants who reduce their consumption by at least one category (eg, from “16 to 20 sticks of cigarettes per day” to “10 to 15 cigarettes per day”) from baseline will be counted as successfully achieving smoking reduction.7-day smoking abstinence at 4-week and 6-week follow-up: At the 4-week and 6-week time points, researchers reviewed and analyzed participants’ (in both groups) smoking status in the past 7 days to identify their 7-day smoking abstinence at both these time points. A 7-day smoking abstinence is defined as not a single cigarette being smoked in the past 7 days [35].30-day self-reported smoking abstinence at 6-week follow-up: At the 6-week time point, researchers will review and analyze participants’ smoking status in the past 30 days to identify their self-reported 30-day smoking abstinence. A 30-day smoking abstinence is defined as not a single cigarette being smoked in the past 30 days [35].

The retention rate of the trial refers to participants providing their daily smoking status at the end of every week.

Program usage will be measured by the number of times participants interact with the assigned versions of the SCAMPI program. At the end of the pilot trial, researchers will review the data on how many times participants like, comment, forward, post content from SCAMPI OA on a personal board, or have a conversation with their friend. The data on the number of times participants used the SCAMPI mini-program (for participants in the intervention group only) and the data on the number of times participants (in both groups) communicated with the program (by sending text messages, voice messages, or emoji) to the SCAMPI OA will also be collected and reviewed. These data may reflect the level of engagement between users in the SCAMPI program.

Users’ satisfaction with the SCAMPI program will be measured by a standard MARS questionnaire at the end of the trial. As some questions on the questionnaire are not applicable to the restricted version of the program, only participants in the intervention group will be requested to complete the questionnaire (Multimedia Appendix 6) [38,39].

### Data Collection

All data of the study will be collected online through the social network platform WeChat. Table 3 shows the schedule of different data collections of the study.

**Table 3 table3:** Schedule of study data collection.

Characteristics		Week 1 (day 0)	Week 1-5 (day 1-35)	Week 6 (day 36-42)
		Screening + baseline data collection + randomization	Follow-up data collection	Follow-up data collection
**General data**				
	Eligibility	✓^a^	—^b^	—
	Electronic consent	✓	—	—
	Demographics	✓	—	—
	Quitting history	✓	—	—
	Smoking cessation interventions usage	✓	—	—
**Primary outcome**				
	Participants’ biochemical verified 30-day smoking abstinence at 6-week follow-up	—	✓	✓
**Secondary outcomes**				
	Cigarette consumption	✓	✓	✓
	7-day smoking abstinence at 4-week and 6-week follow-up	—	✓	✓
	30-day self-reported smoking abstinence at 6-week follow-up	—	✓	✓
	Participants’ retention	✓	✓	✓
	Program usage	—	✓	✓
	Users’ satisfaction with the program (intervention group)	—	—	✓

^a^Data were collected in the described timepoint.

^b^Data were not collected at the described timepoint.

Screening data will be collected at week 1 (day 0) via the registration questionnaire to determine eligibility for all individuals who read the study advertisement and entered the study registration system. The questionnaire consists of a short overview of the aim of the study and questions regarding the person’s demographics, additions, quitting history, willingness to quit, and the usage of other smoking cessation interventions. All questionnaires of the trial were delivered by the Tencent Questionnaire platform, which is compatible to the WeChat platform.

Data on participants’ cigarette consumption will be collected from day 1 to day 42 of the study via the same questionnaire platform. At the end of each week, participants will be provided with a link through WeChat messages to have access to the corresponding online questionnaire to enter their cigarette consumption status on each day of the week.

Users’ satisfaction with the SCAMPI program (intervention group only) will be collected on day 42 along with the last weekly cigarette consumption status checking questionnaire. Data collected through online questionnaires will be downloaded from the platform and stored in a secure university server after every collection.

The program usage data (both versions) will be recorded by the WeChat mini-program and OA databases. These data will be exported and stored in the same place as data collected from online questionnaires.

On day 42, a link of ShunFeng courier WeChat mini-program will be sent to participants who self-reported themselves as 30-day smoking abstinence. Participants who received the link were requested to provide their address and recipient details to the courier through WeChat (none of these data were accessible or recorded by the research team). On the basis of the provided details, the kits with instructions will be sent to participants. Participants were requested to use the kit as instructed, take a photo or shoot a short video about how they used the kits and the relevant results (personal images were not asked), and send the test results to the SCAMPI OA.

### Data Management

The National Institute for Health Innovation, University of Auckland, is responsible for storing and protecting the research data. As a digital trial, all data will be entered electronically. All electronic data will be stored on the university computer with password protection. Only the principal investigator and members of the research team will have access to the computer-based data. All participants will be assigned a specific code number to protect their confidentiality. All data will be under the unique code number and stored for a period of 3 years after completion of the study.

### Statistical Methods

Data from this study will be exported from different databases, the WeChat mini-program and OA databases for the data related to the SCAMPI program usage and the Tencent Questionnaire database for the data related to participants’ demographics, additions, quitting history, willingness to quit, the usage of other smoking cessation interventions, and cigarette consumption during the study.

Baseline data collected from all participants will be summarized and presented. Continuous variables (eg, age) will be presented as numbers observed, means, and standard deviations. Categorical variables (eg, marital status) will be presented as frequencies and percentages. As any differences between randomized groups at baseline could only have occurred by chance, no formal significance testing will be conducted. Primary and secondary outcomes will be summarized descriptively at the identified time points. A generalized linear mixed model will be used to assess the effect of the SCAMPI program on participants’ smoking cessation outcomes.

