### Power

We determined the power for the proposed main trial of this study. A total sample size of 530 (265 per group) will have 90% power at 5% significance (two-sided) to detect an absolute difference of 10% on the primary outcome between the 2 groups, assuming a control rate of 6.7% [19] and 20% loss to follow-up. Given the budget and resource limitations, in this study, we aim to recruit around (80/530, 15.1%) of the total sample size required for the main trial, that is, n=80 (40 per group), using an open recruitment strategy to recruit all participants within a month. At the end of the study, we will re-estimate the power of the final percentage differences between groups in the effectiveness report to further determine the exact final sample size of a full trial. The sample size is considered as a major limitation of the study.

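### The mixed model is not excepted for the primary outcome, which is one yes/no value per person, so its variance is not identifiable and its odds ratio can depend on the software

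*Protocol article*

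**What the plan says.** The Statistical Methods section of the protocol article names one inferential method for the smoking cessation outcomes: "A generalized linear mixed model will be used to assess the effect of the SCAMPI program". It does not state the random effect, link function or covariates, and it sets no outcome apart. The same section says that primary and secondary outcomes will be summarized descriptively.

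The Primary Outcome Measure section fixes the endpoint: "The primary outcome of this pilot trial will be the participants’ biochemical verified 30-day smoking abstinence at 6-week follow-up". It is binary, because "Quit failure was defined as any cigarettes smoked in the past 30 consecutive days". Verification is triggered once, as the Data Collection section says: "On day 42, a link of ShunFeng courier WeChat mini-program will be sent to participants who self-reported themselves as 30-day smoking abstinence".

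Randomization and Allocation describes individual 1:1 randomization. Study Setting describes one online platform and names no sites or groups. Retention counts dropouts and those lost to follow-up as smoking. Among the abstinence outcomes, only "7-day smoking abstinence at 4-week and 6-week follow-up" has more than one value per person. Cigarette consumption is also reported repeatedly, in weekly questionnaires.

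The Power section plans the main trial "to detect an absolute difference of 10% on the primary outcome between the 2 groups", with a control rate of 6.7% and 20% loss to follow-up. It sets the pilot at 40 per group and says that the percentage difference observed in the pilot will be used to fix the final main-trial size.

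**The concern.** A mixed model is for observations that are correlated within some unit. The only unit that the article describes is the participant, and each participant contributes exactly one value to the primary outcome. The missing-data rule completes this: nobody lacks a value, so even the common missing-data reason for a mixed model is absent.

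Two arm proportions are then all the information there is. They support two parameters (an intercept and a treatment effect), but not a variance as well. At stake is the headline effect estimate for the primary outcome. A conditional odds ratio whose size depends on an inestimable standard deviation, or on the numerical approximation used, is a poor basis for judging preliminary effectiveness. It is also on a different scale from the percentage difference on which the main trial is planned.

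**Working it through.** **Inputs.** Control rate 6.7%, difference 10 points (so 16.7% in the intervention arm), 20% loss, 90% power, two-sided 5% and 40 per group, all from Power. One binary value per person, from Primary Outcome Measure. Assumed, because the article does not state them: a logit link and a participant random intercept.

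**1. The plan's own figure.** With unpooled variance, n per arm = (1.960 + 1.282)² × (0.067 × 0.933 + 0.167 × 0.833) / 0.10² = 211.9. Dividing by 0.80 gives 264.8, that is 265 per arm and 530 in total. The stated size is reproduced, so the rates are read as intended. The figure of 530 is not in question.

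**2. Identifiability.** With random-intercept SD σ, the probability of abstinence in an arm is the average of 1/(1 + exp(−(η + σu))) over a standard normal u. For any σ, a value of η can be found that gives any chosen arm proportion. The exact likelihood depends on the data only through the two arm proportions, so it is the same at every σ.

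Solving for η in each arm at 6.7% and 16.7% by Gauss-Hermite integration:

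| σ | Conditional odds ratio |
|---|---|
| 0 | 2.79 |
| 1 | 3.12 |
| 2 | 4.27 |
| 3 | 6.51 |

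At σ = 0 this is (0.167/0.833) / (0.067/0.933) = 2.79.

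For the nearest whole-number table, 3/40 vs 7/40, the exact log-likelihood is −29.204 at σ = 0, 0.5, 1, 2, 3 and 5. The marginal odds ratio stays at 2.62, while the conditional odds ratio runs 2.62, 2.68, 2.91, 3.95, 5.90 and 14.70.

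**3. Dependence on software.** Under a Laplace approximation the same table does not give a flat likelihood. It rises from −29.20 at σ = 0 to −26.75 at σ = 3 and −20.08 at σ = 8. A program using that approximation is drawn towards a large variance that the data do not support.

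**4. Sparse events, a separate matter.** Expected events are 40 × 0.067 + 40 × 0.167 = 2.68 + 6.68 = 9.36. If the rates held only among the 80% retained, 32 × 0.234 = 7.5. If both arms were at 6.7%, 80 × 0.067 = 5.4. The probability of no control event is 0.933⁴⁰ = 6.2%, and then the maximum-likelihood odds ratio is infinite. In simulated trials with events in both arms, the ordinary odds ratio ranges from 0.65 to 11.3 (central 95%).

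**5. What a direct analysis gives.** For 3/40 vs 7/40 the difference is 10 points, with a Newcombe 95% CI of −5.1 to +25.3 points. It is wide, but uniquely defined and on the scale that the Power section uses.

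**The case against.** The strongest reply is that the article names no random effect, link or covariates, and that such structure is commonly left to an analysis plan. The model sentence covers the cessation outcomes collectively, and a mixed model suits several of them. This stands in part: the odds ratios above rest on an assumed specification. But the choice of model class is stated, the primary outcome is not excepted, and no participant-level intercept in a logit model becomes identifiable with one binary value each. Table 3 does mark the primary outcome in both follow-up columns. Those entries reflect the daily reports that feed the 30-day window; the outcome itself is still one value.

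A second reply is that the harm is narrow, and this stands. The fitted arm proportions do not change with σ. Under the exact likelihood, neither does the likelihood-ratio test: for 3/40 vs 7/40, 2 × (30.14 − 29.20) gives a chi-square of about 1.87, p about 0.17. If the variance goes to zero, the analysis is ordinary logistic regression. The plan does not ensure that outcome, and the Laplace result shows that it need not occur.

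Two stronger readings are tempting, and the document supports neither:

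- A reader might infer that the absolute difference will not be produced. Statistical Methods plans descriptive summaries and Power plans to use the percentage difference. Only an interval for it is not supplied by the named model.
- A reader might infer that the low event count causes the identification failure. It does not. One value per person causes it, at any sample size. Sparsity follows from the pilot's size, which the article itself acknowledges as a limitation, and it would trouble ordinary logistic regression too.

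**Conclusion.** The point holds at moderate severity. As written, the only named inferential method extends to a primary outcome that it does not fit. Under a logit link and a participant intercept, the variance is not identifiable. The conditional odds ratio for the planning rates moves from 2.8 to 6.5 as the SD goes from 0 to 3, with no change in fit. The article gives no value for the SD, so this range shows sensitivity and does not predict the reported result. The same applies to self-reported 30-day abstinence at week 6. It does not apply to the repeated outcomes.

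The event count of about 9 borrows the main-trial planning rates, because the pilot states none of its own. It adds instability but is a separate issue. The pilot's arm percentages remain interpretable whatever the model does, which is why this is not graded higher.

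**What to change.** In Statistical Methods, separate the outcomes by the number of values per person:

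- **Verified and self-reported 30-day abstinence at week 6:** replace the mixed model with the risk difference and a score-type 95% CI (for example Newcombe or Miettinen-Nurminen) on all 40 per arm, counting dropouts as smoking as already planned. If a p-value is given, use an exact test.
- **7-day abstinence at weeks 4 and 6, and weekly consumption:** keep the generalized linear mixed model, and say that its random effect is the participant.

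A further stratified analysis is not advised, because it would divide about 9 events into smaller cells. The cost is a few sentences. No new data are needed, and the interval serves the main-trial sizing decision directly.
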